#### Participant flow/ procedure

Figure 1 illustrates the study flowchart.

**Fig. 1 Fig1:**
[figure not shown]
Study flowchart

#### Data collection methods

##### Participant identification

The main strategy for recruitment is to contact those social care provider organisations. Social media advertising will be utilised. Local ID charity organisations and parent carer fora (through the National Parent Carer Forum) will also be contacted. It is expected that settings for people likely to be eligible (those with mild to moderate ID) are most likely to be individual (with their family, or in independent living). Thus, a cluster randomised design is unlikely to be relevant. However, as there is a small risk of contamination in group settings using this design, only one adult with ID and their support worker per group setting will be recruited. During recruitment, a record will be kept of the number of instances in which there is more than one person eligible and interested in taking part within the same setting. This issue will also be explored in the qualitative interviews with support staff working in group settings. These data will inform the choice of research design for a future definitive trial.

##### Screening, recruitment and consent

In order to detect any biases from differential recruitment, a log of all participants considered/approached, including details of the recruitment pathway (via social media or via provider agencies) and whether they are ineligible or eligible will be completed. Provider agencies will be asked to complete a log of the number of potential participants they contact about the study. Both the adult with ID and their family carer/support worker will be consented into the study. There will be two versions of the participant information sheet (PIS), one will be provided to the family carer/support worker and one will be a version utilising images to assist with understanding will be provided to the adult with ID (participant). The participant and family carer/support worker will have been sent the participant information sheet and consent form prior completing any measures and given sufficient time to discuss the information with their support worker/family carer. The study will be explained in detail, including randomisation and consent for long-term follow-up. A placement assessment that is provided by HER® to assess where within the intervention the individual is best advised to start will be used for eligibility screening across all participants prior to baseline data collection. Consent will be gained for this eligibility assessment. If a participant is happy to take part, informed consent will be obtained. Consent will be taken either face-to-face or via videoconferencing. The study research assistant (S-RA) will read aloud each statement of the consent form and ask the participant to agree to each statement and approve that each one is signed individually. The S-RA will then sign on the participants’ behalf if this process is completed virtually. Once consent is gained, the following will be completed:A contacts form will be completed for participants including multiple methods of contact (address, telephone, email address) to minimise loss to follow-up.Baseline data collection completed (either at time of recruitment or at a suitable time for the participant). This will either be completed face-to-face or virtually via teleconferencing.

The addition of the option of completing consent and data collection virtually was included as a result of COVID-19 restrictions.

#### Randomisation

Participants will be randomised following screening and completion of baseline assessments. Participants will be randomised in a 1:1 ratio using a block randomisation programme developed by the Centre for Trials Research (CTR). Allocations will be balanced by setting type (family home vs. other social care setting). Participants will be randomised to READ-IT in addition to usual practice or Usual Practice alone (i.e. for their reading from those within their care environment). The research assistant providing on-going intervention support (this must not be the S-RA collecting baseline and follow-up data as they should remain blind to allocation, the intervention research assistant (I-RA)) will inform participants and their support workers/family carers of their allocation by telephone and will provide all details of starting the READ-IT programme to those allocated to the intervention arm. Randomisation will be performed by the study manager/data manager who will inform the I-RA of the allocation prior to their telephone call with the participant. Given that no more than one individual from a group setting will be recruited to the study, there is no danger of participants from the same setting being randomised into different trial arms, limiting the risk of contamination.

#### Frequency and duration of follow-up

Data will be collected at 6 months post-randomisation. Participants will be contacted by the S-RA to complete this face-to-face or via teleconferencing. To reduce the risk of bias, the S-RA will read questions from the questionnaire directly, remain blind to the participants’ allocation and will ask participants not to reveal their allocation. If allocation is revealed, this will be noted.

#### Process evaluation

A process evaluation will be based on the MRC framework [32] and will incorporate data from the interviews, recruitment pathways and fidelity/adherence data to examine five key aspects of the feasibility of conducting a definitive trial of HER® for adults with ID: (1) intervention recruitment, adherence and reach; (2) intervention implementation; (3) intervention mechanisms, including receipt and acceptability; (4) the impact of COVID-19 on service as usual and (5) the feasibility of implementing HER® within a definitive RCT.

#### Data management and security

Study data will be entered on to paper case report forms (CRFs) by the S-RA at the time of data collection and subsequently entered on to a MS Access Database directly by the S-RA. A sample of CRFs will be scanned and checked visually on receipt by the study administrator, data manager or study manager. RAs will be trained in good clinical practice (GCP) and study specific processes. Hard copies of personally identifiable and research data will be held separately and securely in a locked cupboard, with access limited to essential research team members. CRFs will be pseudonymised and data entered manually onto a secure, password-protected Microsoft SQL database by the study administrator (SA) and data queries noted. Ten percent of all data will be quality checked and all data queries actioned by the data manager (DM). Any key data queries will be taken to the study management group (SMG) or SSC as appropriate. Wherever possible, data will be validated at point of entry, thereby reducing the opportunity for missing or unexpected data. All changes made to the data will be recorded and visible via an audit log within the database. Finally, data will be checked during data cleaning using SPSS syntax for validations and missing data. Qualitative interviews will be conducted remotely, recorded via the encrypted services offered by the platform used and stored on password-protected computers at site. Recordings will be securely transferred to the study team at the CTR by Fastfile or courier. All files will be encrypted and transcripts will be fully pseudonymised prior to analysis. Data security and confidentiality will be ensured, in line with GDPR. A data management plan will be completed and adhered to. Only the trial team will have access to the final study dataset.

#### Statistical methods/analysis plan

The majority of outcome analysis will be descriptive in nature. Continuous data will be reported as means and standard deviations, or medians and interquartile ranges, as appropriate. Categorical data will be reported as frequencies and proportions. All data will be reported both overall, per arm and by setting type. Outcomes will be estimated with their associated 95% confidence intervals. No formal hypothesis testing will take place. A detailed statistical analysis plan will be written and agreed by the study management team prior to any analysis taking place. The estimates obtained from the feasibility questions will be used to inform the design, sample size, randomisation strategy and analytical approach for a definitive effectiveness study. The findings from the study will be reported in line with the CONSORT extension for pilot and feasibility studies [33].

#### Cost effectiveness methods/analysis plan

Whilst no formal economic analysis will take place, consideration will be given to the practicalities and difficulties associated with collection of quality of life and CSRI data that would be needed in a future trial.

#### Qualitative methods/analysis plan

Semi-structured qualitative interviews will be conducted with a selection of adults with ID, support workers and family carers delivering READ-IT, after the 6-month follow-up assessment. Sufficient interviews will be conducted to achieve ‘information power’ [34] which focuses on the quantity and quality of information gathered relevant to the research question rather than sample size, but is likely to include 8 to 12 adults with ID with similar numbers of support workers and family carers. Thematic analysis as outlined by Braun and Clarke [35] will be used to analyse the data, with a focus on identifying patterns of shared meaning.

#### Progression criteria for a definitive trial

Criteria will inform the decision to progress to a definitive trial, with consideration to issues that may have affected meeting any of these criteria and steps that can be taken to overcome these issues within a full trial. These will be based on a traffic light system with green indicating ‘go without any modification necessary’; amber indicating ‘potential proceed to definitive trial, remedying early issues’; red indicating ‘stop’.**Participant recruitment**: % of participants approached, and who are eligible, consent to the study (and thus are willing to be randomised)Green ≥50%Amber 30≥<50%Red <30%**Individual randomisation possible** (% of total number of settings in which more than one participant is eligible and willing to take part) (NB. Amber/red here may lead to a proposal for a cluster randomised design)Green ≤20%Amber 20>≤40%Red >40%**Rate of recruitment**: % of recruitment target (48 participants) are recruited within the study recruitment periodGreen 100%Amber 70≥<100%Red <70%**Participant retention**: % of participants retained 6 month follow-up data collection timepointGreen 75<>100%Amber 50≥<70%Red <50%**Usual practice**: % of participants in the UP arm of the study who receive an alternative structured programme designed to teach them to read between baseline and 6 month follow-upGreen ≤30%Amber 30>≤50%Red >50%**Fidelity**: Self-rating forms indicate % of READ-IT manual components have been met both across and within sessions.Green 70<>100%Amber 50≥<70%Red <50%**Adherence**: % of participants and their support workers/family carers who adhere to the READ-IT programme (attend training, complete 80 episodes within 20 weeks, meet adherence criteria built into HER® programme)Green >70%Amber 50≥<70%Red <50%**SSC consensus**—considering all progression criteria, feasibility study findings and evidence of whether progression criteria not met can be mitigated, a clear majority of the SSC independent members recommend progression to a definitive trial

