#### Sample size calculation

A total of 48 individuals will be recruited (randomising 24 per arm). As this is a feasibility study, and the purpose is to provide estimates of key parameters for a future trial rather than to power the current study to detect statistically significant differences, a formal a priori power calculation will not be conducted [31]. However, recruiting 48 participants will provide a certain level of precision around a 95% confidence interval. For example, if 80% of participants provide outcome data at follow-up, the 95% confidence interval around the percentage can be estimated within +/− 11% (i.e. 69 to 91%).

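### The retention progression criterion gives no traffic-light category to results from 70% to under 75%

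*Protocol article*

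**What the plan says.** The section Progression criteria for a definitive trial sets out seven criteria with numerical bands, followed by a consensus item for the SSC. The scheme is introduced with "These will be based on a traffic light system with green indicating ‘go without any modification necessary"; amber means that a definitive trial may still go ahead once problems are remedied, and red means stop.

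For retention the bands are "retained 6 month follow-up data collection timepointGreen 75<>100%Amber 50≥<70%Red <50"%. For comparison, fidelity has "Green 70<>100%Amber 50≥<70%Red <50"% and adherence has "Green >70%Amber 50≥<70%Red <50"%.

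The final item asks whether "a clear majority of the SSC independent members recommend progression to a definitive trial", after weighing all the criteria and whether any shortfall can be mitigated.

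Two statements under Sample size calculation bear on the size of the problem: "A total of 48 individuals will be recruited (randomising 24 per arm"), and "if 80% of participants provide outcome data at follow-up, the 95% confidence interval around the percentage can be estimated within +/− 11% (i.e. 69 to 91"%). The second uses follow-up completeness as its worked example, so it supplies the only retention rate given anywhere in the article.

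**The concern.** A traffic-light rule is useful because every possible result has its category fixed before the data are known. Here the upper limit of amber (70) and the lower limit of green (75) are different numbers, so the range between them belongs to neither.

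If retention fell in that range, the choice between calling it satisfactory and calling it a problem to be remedied would be made with the result in hand. The article tests no hypotheses and lists retention among the measures for its secondary objective, the feasibility of a definitive trial. Under Stage 3, a full-trial protocol depends on the progression criteria being met. The retention category is therefore one of the study's main outputs.

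**Working it through.** **Inputs.** The denominator is n = 48 and the illustrative retention is 80% (both from Sample size calculation). Retention bands, from the progression criteria: red below 50%, amber from 50% to below 70%, green from 75% to 100%.

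**1. The article's own figure.** The Wald half-width is 1.96 × √(0.80 × 0.20 / 48) = 0.113, giving 68.7% to 91.3%. This reproduces the stated ±11% (69 to 91%). The whole range from 70% to 75% lies inside that interval.

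**2. Is the gap peculiar to retention?** The cut-points at which green meets amber are:

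| Criterion | Green limit | Amber limit |
|---|---|---|
| Recruitment | 50% | 50% |
| Individual randomisation | 20% | 20% |
| Rate of recruitment | 100% | 100% |
| **Retention** | **75%** | **70%** |
| Usual practice | 30% | 30% |
| Fidelity | 70% | 70% |
| Adherence | 70% | 70% |

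Six criteria share a common number. Retention does not.

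**3. Which results are affected?**
- 33/48 = 68.8%: amber
- 34/48 = 70.8%: no category
- 35/48 = 72.9%: no category
- 36/48 = 75.0%: green, reading the band as 75 to 100

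The gap does not depend on recruiting exactly 48. A range of width 0.05 that includes its lower end must contain at least one count k/n once 0.05 × n ≥ 1, that is, for any n of 20 or more.

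**4. How likely is it?** P(34 or 35 retained) = Σ C(48, k) pᵏ (1 − p)⁴⁸⁻ᵏ over k = 34 and 35.

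| True retention p | Source of p | P(unclassified) |
|---|---|---|
| 70% | assumed | 0.241 |
| 75% | assumed | 0.223 |
| 80% | the article's example | 0.104 |
| 85% | assumed | 0.018 |

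At 80% the full split is amber (24 to 33 retained) 0.044, unclassified 0.104, and green (36 or more) 1 − 0.044 − 0.104 = 0.852, with negligible probability of red.

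**5. Effect of closing the gap.** With a single cut at 75%, 34 and 35 become amber. With a single cut at 70%, they become green. The two repairs give opposite labels to exactly the results in question.

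**The case against.** The strongest reply is that little hangs on this. The gap separates only green from amber, both of which allow progression, and the stop boundary at 50% is clear. The criteria are meant to inform a judgement, and the SSC item provides for one. At the article's own 80%, about nine results in ten are classified. All of this stands, and it limits the consequence. It does not remove the defect: the SSC item weighs the criteria together but does not say what colour 34 or 35 out of 48 receives. A reader might infer that a result in the gap leaves the study with no planned route to a decision. That goes too far, since only the retention label is undefined.

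A reader might also take the signs in the green band literally and conclude that exactly 75% and exactly 100% retention fall outside green. Counting 36/48 as unclassified would raise the probabilities to 34%, 36% and 20% at true rates of 70%, 75% and 80%. The text does not support this. Elsewhere in the same list a sign placed after the first number applies to that number: in the amber band for retention it means at least 50 and below 70. By that convention the green band would mean below 75 and above 100, which is empty. It can only be shorthand for 75 to 100. The same holds for the fidelity band, so holes at exactly 70% or 100% fidelity are not established either.

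As printed, adherence does omit exactly 70%, but no planned count produces it: 0.70 × 24 = 16.8 for the intervention arm (16/24 = 66.7%, 17/24 = 70.8%), and 0.70 × 48 = 33.6 for the whole sample.

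**Conclusion.** The point holds for retention from 70% to under 75%. The two printed limits differ, so no reading of the inequality signs closes the gap, and nothing else in the article does so.

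At the planned size it affects two attainable results, 34 and 35 retained. The probability of one of them is about 10% at the article's illustrative 80%, 22% to 24% if true retention is 75% or 70%, and 2% at 85%. These figures assume 48 participants in the denominator and independent retention with a common probability. Only the 80% rate comes from the article.

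What is at stake is whether retention is reported as needing no change or as needing a remedy. No estimate is biased and the stop rule is unaffected. It is a plain error in a stated decision threshold, modest in consequence, and best corrected before the retention result is known.

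**What to change.** Before follow-up data are seen, the sponsor and the SSC should reconcile the two limits and record one common green/amber cut-point for retention. There are two consistent choices:

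- green ≥75%, amber ≥50% to <75%, red <50% (the more cautious choice); or
- green ≥70%, amber ≥50% to <70%, red <50% (in line with the fidelity and adherence cut-points).

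The article does not reveal whether 70 or 75 was the slip, so those responsible must say which they intended. Writing the green band for fidelity and adherence as ≥70% would be a tidy but optional change of wording.

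The cost is one corrected number and a recorded SSC agreement. It needs no extra data, participants or analysis.

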#### Eligibility criteria

##### Inclusion criteria

Adults administratively defined as having an ID (i.e. through receipt of/being known to services) who:have the capacity to give informed consenthave a level of competence in understanding English suitable to access Headsprout® Early Reading programme. This is assessed via a placement assessment that is provided by HER® to assess where within the intervention the individual is best advised to start and assesses upper-reading ability.can sound out words (although *degree* of articulation will not be a factor). (Sounding out words is a requirement of the HER® component of the intervention).have access to appropriate internet-enabled technologyeither have basic mouse skills, or the capacity to be taught basic mouse skillsare living in a setting in which they are getting daily living skills support supported by a support worker/family carerhave access to a supporter who is themselves able to read and willing to support the individual for the duration of the study

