The HER® programme consists of 80 online episodes delivered in sessions of approximately 20‑25 min. HER® recommends between 3 and 6 sessions of 20 to 25 min per week. READ-IT will therefore be delivered on average 16‑20 weeks. Following recruitment and randomisation, support workers/family carers in the intervention group will be invited to attend a half-day remote training workshop. The purpose of training will be to demonstrate how the HER® online programme works and how the support manual can be used by support workers/family carers to help the person that they are supporting. Two options for training dates each month will be offered. Support workers and carers will be given a copy of the support manual and a unique code to access the HER® programme. All support workers and family carers will, in addition, be offered bi-weekly phone-in help sessions over the duration of the intervention. The intervention for each participant will begin once their support worker/family carer has completed the training.

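### The adherence criterion demands all 80 episodes, yet placement may advise a later start; if that advice is followed, compliant later starters are scored non-adherent

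*Protocol article*

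**What the plan says.** Under *Progression criteria for a definitive trial*, adherence is the percentage of participants and their supporters who satisfy three components: "attend training, complete 80 episodes within 20 weeks, meet adherence criteria built into HER® programme". Green is above 70%, amber is 50% to below 70%, and red is below 50%.

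Under *Intervention*, "The HER® programme consists of 80 online episodes". The 80 episodes required for adherence are therefore the entire programme.

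Under *Inclusion criteria*, the HER placement assessment is described as serving "to assess where within the intervention the individual is best advised to start and assesses upper-reading ability". Under *Screening, recruitment and consent*, the same assessment "to assess where within the intervention the individual is best advised to start will be used for eligibility screening across all participants", before baseline data are collected.

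No section adjusts the episode count for a participant advised to start after episode 1. No section says that everyone starts at episode 1 whatever the assessment shows.

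**The concern.** An assessment that advises a starting point allows starting points to differ. A participant who follows advice to begin at, say, episode 21 has 60 episodes to do. That participant cannot complete 80, however well the carer or support worker delivers the programme.

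The primary objective is whether family carers and support workers can deliver READ-IT. Adherence and fidelity are the traffic-light criteria that speak to it most directly. As worded, a low adherence figure could mean that delivery failed, or that several participants read well enough on entry to be placed further on. The percentage alone cannot separate the two. If the meaning of completion is settled only after the results are known, the criterion also loses the protection of being fixed in advance.

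**Working it through.** **Inputs**
- Intervention arm: 24 (*Sample size calculation*: "A total of 48 individuals will be recruited (randomising 24 per arm"). I take all 24 as the denominator.
- Programme length: 80 episodes (*Intervention*).
- Green above 70%, red below 50% (*Progression criteria*).
- Share starting after episode 1: not given. It is treated as an unknown, q, and shown over a range.

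**The plan's own figure.** *Intervention* derives an average delivery period of 16 to 20 weeks. This reproduces as a full course at 4 to 5 episodes a week: 80/5 = 16 and 80/4 = 20. The figure fits everyone doing all 80 episodes, and this counts in the plan's favour (see the objection).

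**Episodes left after a later start.** A start at episode s leaves 81 − s episodes:
- s = 1: 80
- s = 21: 60
- s = 41: 40

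Only s = 1 can satisfy a literal count of 80.

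**Break points.** Green needs the smallest x with x/24 > 0.70. Since 16/24 = 66.7% and 17/24 = 70.8%, x = 17. If k of 24 start later, the highest attainable adherence is (24 − k)/24:
- k = 7: 17/24 = 70.8%, green only if every remaining dyad adheres
- k = 8: 16/24 = 66.7%, green impossible
- k = 12: 12/24 = 50.0%, still amber
- k = 13: 11/24 = 45.8%, red whatever the delivery

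**Below the break points.** The chance of green is P(X ≥ 17) with X binomial, n = 24. Three success probabilities are compared:
- 1 − q: literal rule, all episode-1 starters adhere
- 0.85 × (1 − q): literal rule, true adherence assumed to be 85%
- 0.85: completion counted from each participant's own start, same assumption

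| q (assumed) | Literal, all episode-1 starters adhere | Literal, 85% true adherence | Counted from own start, 85% |
|---|---|---|---|
| 10% | 0.998 | 0.82 | 0.98 |
| 20% | 0.91 | 0.48 | 0.98 |
| 30% | 0.57 | 0.18 | 0.98 |
| 40% | 0.19 | 0.04 | 0.98 |
| 50% | 0.03 | 0.005 | 0.98 |

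The 85% and every value of q are assumptions chosen for illustration. At q = 10% the loss is modest, and at q = 0 there is none.

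**The case against.** The best defence is that the protocol never says participants will skip episodes. The placement tool is described by its general purpose. Its stated uses in this trial are eligibility: enough English to access the programme, and exclusion of readers who are too proficient. The delivery section describes an 80-episode course, its 16 to 20 weeks fit that course, and the adherence rule matches it. On that reading everyone does the full programme and the rule misclassifies nobody. This stands as a possible reading. It is not stated, however, and it sits awkwardly beside an assessment that advises where to start.

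A related defence is that the study targets adults without basic reading skills, so few may be placed late. That may be so. The documents neither confirm nor exclude it.

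A reader might infer that a red result would wrongly stop the programme. The documents do not support that. The same section says the criteria inform the decision, allows for circumstances that affected them, and ends with a majority view of the steering committee's independent members on whether shortfalls can be mitigated. The process evaluation and interviews also bear on delivery. This removes the automatic consequence. It does not make the percentage itself interpretable.

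It could also be said that a fidelity framework or analysis plan will define completion. Detail may well sit there, but the article has already fixed the number at 80, so this is a stated rule and not an omission.

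**Conclusion.** The point holds conditionally. If placement advice is followed, the adherence rule as written scores every later starter as non-adherent even with perfect delivery, and so mixes reading level at entry with delivery. With 24 in the arm, green needs 17, becomes unattainable at 8 or more later starters (33%), and gives way to forced red at 13 or more (54%).

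This rests on two assumptions: that some participants do start after episode 1, and that 80 is read as a count and not as reaching the end of the programme. The share placed later is unknown, so the effect could be nil or decisive. It would go too far to say that green will be missed or that progression will be halted. The supportable conclusion is that the sections on eligibility, screening, intervention and progression need reconciling. The change is worth making before data are seen because it costs almost nothing. The sample-size precision statement is unaffected.

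**What to change.** Reconcile *Inclusion criteria*, *Screening, recruitment and consent*, *Intervention* and the adherence criterion before outcome data are seen, in one of two ways. Which one reflects the intended delivery is for the trial team to say.

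1. State that all participants start at episode 1 and that the placement assessment serves eligibility only. The count of 80 then stands.
2. Keep the criterion as a percentage of dyads, and count the episode component as met when a dyad completes every episode from its recorded placement point to episode 80 within the stated window. Training attendance and the HER built-in criteria stay as they are.

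In either case, record the placement episode at screening and report adherence alongside it.

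The cost is a sentence or two of text and one field on the screening form. The assessment is already given to everyone, so no visit or participant is added. The second option has a small downside: later starters have less to do in the same time. Over 20 weeks, a start at episode 1 needs 80/20 = 4 episodes a week, at episode 21 it needs 60/20 = 3, and at episode 41 it needs 40/20 = 2. Reporting adherence by placement point keeps that visible.
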